**Methods:**

The HONEY trial will be conducted within the Utrecht cohort for Multiple BREast cancer intervention studies and Long-term evaluation (UMBRELLA). Within UMBRELLA, breast cancer patients referred for radiotherapy to the University Medical Centre Utrecht are eligible for inclusion. Patients consent to collection of clinical data and patient-reported outcomes and provide broad consent for randomization into future intervention studies. Patients who meet the HONEY in- and exclusion criteria (participation ≥ 12 months in UMBRELLA, moderate/severe breast or chest wall pain, completed primary breast cancer treatment except hormonal treatment, no prior treatment with HBOT, no contraindications for HBOT, no clinical signs of metastatic or recurrent disease) will be randomized to HBOT or control group on a 2:1 ratio (*n* = 120). Patients in the control group will not be informed about participation in the trial. Patients in the intervention arm will undergo 30–40 HBOT treatment sessions in a high pressure chamber (2.4 atmospheres absolute) where they inhale 100% oxygen through a mask. Cohort outcome measures (i.e., physical outcomes, quality of life, fatigue, and cosmetic satisfaction) of the HBOT group will be compared to the control group at 3 months follow-up.

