### Randomization and informed consent

In addition to the primary endpoints, other effects for the patients receiving hyperbaric oxygen therapy (i.e., tissue oxygenation, side effects of HBOT, physician-reported outcomes) will be important to evaluate. As a large effect was assumed, the sample size needed to demonstrate a significant effect was rather small. Therefore, in order to be able to answer secondary research questions, a 2:1 ratio for HBOT vs. control group randomization was applied to increase the size of the intervention arm.

A computer-generated randomization list with varying block sizes (*n* = 3–6) will be generated by an independent data manager prior to the first inclusion. Randomization will be stratified for time since inclusion in the UMBRELLA cohort (i.e., ≤ 2.5 years or > 2.5 years after start radiotherapy). The randomization list is linked to a specially designed inclusion database in Microsoft Access. The investigator has no access to the randomization list. After enrolment in the inclusion database, Microsoft Access will allocate patients to their respective treatment.

In accordance with the TwiCs design, patients randomized to the HBOT arm will be contacted by the investigator and offered to undergo HBO treatment. If they agree, they sign a second informed consent form in addition to the previously signed informed consent form of the cohort. Also, patients have the option to consent for the use of their clinical data for other studies on the same subject. In case patients drop out after providing informed consent, patients are asked for permission for the use of their clinical data in the trial. This trial does not involve collecting biological specimens for storage. The informed consent form is available from the corresponding author upon request. Patients who refuse the offer to undergo HBOT will receive treatment as usual, i.e., standard follow-up. Standard follow-up may entail physiotherapy, edema therapy, and/or analgesics, depending on the patient’s needs. Patients who are allocated to the control arm will not be informed about the HONEY trial, and undergo standard follow-up. For logistic reasons and planning of HBOT, patients will be recruited in batches (Fig. 2). After confirmation of diagnosis by a radiation oncologist, patients provide informed consent and will be referred for hyperbaric oxygen therapy.

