### Hyperbaric oxygen therapy group

The combination of high pressure and 100% oxygen inhalation induces neovascularization and regeneration in the irradiated (hypoxic) tissue [4]. During HBOT, patients are seated in a hyperbaric chamber in which the pressure will be raised from 1.0 atmospheres absolute (ATA) to 2.4 ATA. Subsequently, 100% oxygen is given through a mask placed over nose and mouth for 20 min. One treatment session of HBOT is divided into 4 parts of maximum 20 min during which patients inhale 100% oxygen. In between these parts, there are small breaks without a mask, to decrease the risk on oxygen toxicity. After the oxygen sessions, the pressure will be decreased to 1.0 ATA.

To make sure patients are eligible for hyperbaric oxygen therapy, patients will be seen by a hyperbaric oxygen therapy physician. If patients are not “fit to dive” (e.g., in case of a respiratory tract infection) in between HBOT sessions or prior to HBOT, the HBO physician might decide to cancel a HBOT session to ensure patients’ safety. In case of missed HBO sessions, the HBO physician will decide whether effectivity of HBOT is endangered. Depending on judgment of the hyperbaric oxygen physician, the HBOT might be canceled or prolonged at the end.

HBOT consists of 30–40 hyperbaric oxygen sessions (i.e., one session of 2 h per day, 5 days/week). There are appointments with the HBO physician scheduled after 15 and after 30 HBO sessions, since the first effects of HBOT on late radiation toxicity will occur after 20–30 HBO sessions. Therefore, the patient and the HBO physician will decide together whether or not an additional 10 sessions will be valuable after 30 HBO sessions, depending on the effects achieved with HBOT so far. In between hyperbaric oxygen sessions, patients in the intervention group might still require edema therapy and physiotherapy or use analgesics (i.e., usual care). All concomitant care is permitted; the use of these treatments will be monitored.

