### Primary and secondary endpoints

The primary endpoint of this study is the difference in proportion of patients with severe/moderate reported breast/chest wall pain between both groups at 3 months follow-up (Fig. 2). Upon inclusion, all patients will have moderate/severe pain, as this is an inclusion criterion. Self-reported pain is assessed through the late radiation toxicity questionnaire on a 4-point Likert scale (i.e., none/mild/moderate/severe). Self-reported pain is dichotomized into none/mild pain and moderate/severe pain.

Secondary endpoints include physical functioning, QoL, cosmetic outcome, physician-reported pain and radiation toxicity, tissue oxygenation, and side effects of HBOT. Physical functioning will be evaluated using the late radiation toxicity questionnaire, containing questionnaires on breast and arm edema, arm mobility, and breast fibrosis. QoL will be assessed by means of the EORTC QLQ-C30 and breast-specific questionnaire EORTC QLQ-BR23 [13]. In the UMBRELLA cohort, QoL is measured upon inclusion (before start radiotherapy), at 3 months, and every 6 months afterwards. Self-reported cosmetic outcome will be assessed using the BREAST-Q questionnaire [15, 16]. Depending on previous surgery, patients fill out a different module (mastectomy/breast conserving therapy/reconstruction) yearly within the UMBRELLA cohort. Side effects will be monitored using the MacFie classification [17].

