The primary outcome will be presented in absolute numbers and proportions. The primary outcome is defined as difference in proportion of patients with moderate/severe pain at 3 months follow-up per allocated treatment arm (i.e., intervention or control group). As pain is measured on a 4-point Likert scale, it will be dichotomized into no/mild pain and moderate/severe pain. Pain response is defined as decrease in pain from self-reported moderate/severe pain to no/mild pain. Differences in pain response will be compared by *χ*^2^ test. As secondary analysis, an unadjusted logistic regression analyses will be performed. In addition, as sensitivity analysis, the logistic regression analysis will be adjusted for age, time since radiotherapy, radiotherapy dose, and smoking. There will potentially be missing data. Assuming that missing values are missing at random, multiple imputation by chained equations for the primary analysis will be used to replace missing values, using 20 imputed datasets [23–26]. In addition, complete case analysis will be performed as sensitivity analysis. Toxicity will be presented as the overall incidence of grade 2–4 toxicity. QoL outcomes will be evaluated at 3 time points: baseline in the UMBRELLA cohort, prior to HBOT, and at follow-up. To account for the intra-subject correlation over time, a mixed model for repeated measurements will be used. In the model, a random intercept and random linear time effect and an autoregressive covariance structure of the first order (AR1) (assuming that the correlation systematically decreases with increasing distance between time points) will be included [27]. Also, fixed effects for treatment arm and an interaction between time and treatment arm will be included, as well as characteristics with imbalances as previously described. Differences with a *P* value < 0.05 will be considered statistically significant.

Given the relatively small sample size of the study, we will not be performing an interim analysis, as it is very unlikely that we will see a highly significant effect of HBOT justifying early stopping of the trial. Also, there is ample clinical evidence that HBOT is safe and associated with a very small risk of mild side effects. Therefore, no side effects are expected that might lead to early termination of the study. Consequently, no interim analysis was planned for this study.

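### The QoL model names only a linear time effect; an arm-by-time interaction in that same time would dilute an HBOT effect that can appear only at follow-up

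*Protocol article*

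**What the plan says.** The Data analysis section of the Protocol article fixes the measurement points: "QoL outcomes will be evaluated at 3 time points: baseline in the UMBRELLA cohort, prior to HBOT, and at follow-up". It then specifies the model: "a random intercept and random linear time effect and an autoregressive covariance structure of the first order (AR1", the latter justified by correlation falling as time points lie further apart. Fixed effects are arm and the interaction between time and arm, "as well as characteristics with imbalances as previously described". The only form of time named is linear, and it is attached to the random effect. The coding of time in the fixed part, the type of AR(1) and the contrast to be reported are not given.

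The spacing follows from other sections:

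- Primary and secondary endpoints puts cohort entry before radiotherapy: "QoL is measured upon inclusion (before start radiotherapy), at 3 months, and every 6 months afterwards".
- The abstract's Methods paragraph requires "participation ≥ 12 months in UMBRELLA".
- Randomization and informed consent stratifies at "≤ 2.5 years or > 2.5 years after start radiotherapy", so the first gap varies by patient. No upper limit is given.
- Hyperbaric oxygen therapy group sets 30–40 sessions at "one session of 2 h per day, 5 days/week".
- Additional measurements intervention group places follow-up 3 months after the last session.

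**The concern.** Two of the three points precede HBOT, so the expected arm difference is (0, 0, δ): nothing at cohort entry, nothing just before HBOT, and δ at follow-up. An arm-by-linear-time term describes something else, namely two lines that diverge steadily from before radiotherapy. Fitted to a late step, it puts part of the effect before treatment, where it cannot exist, and reports a diluted slope.

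Two smaller points in the same text add to this. An AR(1) by visit order would treat a gap of a year or more and a gap of about five months as equal steps, against its own stated rationale. And the covariates with imbalances are said to be already described, but the article contains no imbalance rule. The only earlier list (age, time since radiotherapy, radiotherapy dose, smoking) is a fixed adjustment set for the logistic regression. As worded, the QoL covariates could be chosen after seeing the data.

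At stake is whether a real QoL benefit is detected and reported at its true size.

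**Working it through.** The plan states no QoL figure to reproduce. The only figure borrowed from it is the evaluable sample size, 72 + 36 = 108.

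**Spacing.** HBOT lasts 30/5 = 6 to 40/5 = 8 weeks. Adding 3 months gives about 4.5–5 months from the pre-HBOT point to follow-up; 5 is used below. The first gap is at least 12 months; 30 months (the stratum cut) and 60 months are assumed as further cases.

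**Unweighted projection.** Fit the arm difference (0, 0, δ) on an intercept and linear time. At t = (0, 30, 35) the mean is 21.667 and the deviations are −21.667, 8.333 and 13.333, with sum of squares 716.67.

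- Slope = 13.333/716.67 = 0.0186δ per month.
- Fitted before HBOT: 1/3 + 0.0186 × 8.333 = 0.488δ.
- Fitted at follow-up: 1/3 + 0.0186 × 13.333 = 0.581δ.
- Change over the treated interval: 5 × 0.0186 = 0.093δ.

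**Weighted projection.** The expected coefficients are (X′V⁻¹X)⁻¹X′V⁻¹(0, 0, δ)′. V has an assumed random-intercept variance of 0.4 and residual variance of 0.6. The AR(1) correlation is assumed at 0.3–0.6, per visit step (visit order) or per 6 months (continuous time).

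| First gap | Covariance | Pre-HBOT (δ) | Follow-up (δ) | Change (δ) |
|---|---|---|---|---|
| 12 mo | unweighted | 0.445 | 0.686 | 0.240 |
| 12 mo | visit-order AR(1) | 0.483–0.528 | 0.701–0.720 | 0.192–0.218 |
| 12 mo | continuous AR(1) | 0.491–0.557 | 0.760–0.843 | 0.270–0.286 |
| 30 mo | unweighted | 0.488 | 0.581 | 0.093 |
| 30 mo | visit-order AR(1) | 0.510–0.533 | 0.585–0.589 | 0.056–0.075 |
| 30 mo | continuous AR(1) | 0.522–0.588 | 0.627–0.711 | 0.105–0.123 |
| 60 mo | unweighted | 0.497 | 0.541 | 0.045 |
| 60 mo | visit-order AR(1) | 0.508–0.521 | 0.542–0.543 | 0.023–0.034 |
| 60 mo | continuous AR(1) | 0.517–0.562 | 0.565–0.617 | 0.048–0.056 |

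The truth in every row is 0, δ and δ. Overall: 0.45–0.59δ before HBOT, 0.54–0.84δ at follow-up, and 0.02–0.29δ over the treated interval.

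**Sensitivity.** A second set of runs took the continuous-time correlation per year instead of per 6 months, a second gap of 0.4 year, and first gaps of 1 year, 2.5 years or spread over 1–5 years, with and without a random slope. It gave 0.49–0.67δ, 0.53–0.90δ and 0.04–0.28δ. The exact figures depend on these assumptions; the pattern does not.

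**Other codings.** With visit number 0, 1, 2 the slope is 0.5δ per visit, with 0.33–0.42δ fitted before HBOT and 0.83–0.92δ at follow-up. With categorical visit, the follow-up minus pre-HBOT contrast recovers 1.00δ.

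**Power.** For an assumed effect of 0.4 SD in 72:36 patients, under the same second set of assumptions, the expected z is 0.8–2.5 for the linear interaction and 2.1–4.2 for the categorical contrast. The categorical value is the larger in every setting tried.

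**Covariance.** Random intercept, random slope (with their covariance) and AR(1) use 5 parameters against the 6 distinct elements of a 3×3 matrix. A rank check gives 5, so the structure is identified but nearly saturated.

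**The case against.** The strongest reply is that the article never says the fixed time effect is linear. That word describes the random effect only. A mixed model for repeated measurements at three named points is compatible with categorical visits, and time coding is often left to an analysis plan. A reader might infer that the interaction cannot estimate the HBOT effect. The text does not support that: with categorical visits the follow-up contrast is unbiased, and even with linear time the interaction is zero in expectation when HBOT does nothing, because the arms are randomised. It is a weak and distorted measure, not an empty one, and it does not inflate false positives.

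A reader might also infer that the covariance model cannot be fitted, or that AR(1) is wrong here in itself. Neither holds. The parameters are identified, a continuous-time AR(1) would match the stated rationale, and a poor covariance mainly affects weights and standard errors. The reference to imbalances may simply be loose wording for the earlier fixed list.

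What remains is that the article does commit to a model: random effects, residual structure, fixed effects and covariates are all stated. The only time variable it names is linear. This is therefore a stated choice that reads badly, not a detail left to another document.

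**Conclusion.** The point stands in conditional form. If the arm-by-time interaction uses the linear time named in the same paragraph, it attenuates an effect confined to follow-up and implies an arm difference before HBOT that does not exist. Under the assumptions tabulated, less than a third of the true effect appears as change over the treated interval, and about half of it appears before treatment. The upper limit of the first gap, the correlations, the variance split and the 0.4 SD effect are assumptions; the order of the three points, the 12-month minimum and the length of the second gap come from the article. The consequence is lost power and a misreported size for secondary QoL outcomes. The primary pain comparison by χ² test is unaffected.

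**What to change.** - State that time enters the fixed part as categorical visit.
- Name the QoL effect: the arm difference at follow-up, adjusted for the pre-HBOT score and the stratification factor. Constrain the arms to be equal before treatment only if that score is taken before randomisation or the offer; the article says only that it precedes HBOT.
- Replace the random slope plus AR(1) with an unstructured 3×3 covariance, or a continuous-time one.
- Replace the covariates with imbalances by the fixed list already given for the logistic regression: age, time since radiotherapy, radiotherapy dose and smoking.

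The change is to analysis wording and adds no planned measurement point. Its cost is a few more fixed-effect and covariance parameters in about 108–120 patients.

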### Sample size considerations

Since moderate/severe pain is an inclusion criteria, all patients will have moderate or severe pain upon inclusion. We assume that 3 months after the last hyperbaric oxygen session, the proportion of patients treated with HBOT suffering from moderate to severe pain will decrease to 30% [5]. Both control patients and patients who refuse HBOT will receive usual care. It is not expected that the offer of HBOT will influence the outcome at follow-up. Consequently, we assume that of the patients receiving usual care, at least 80% will be reporting moderate/severe pain at the same time point.

It is expected that 50% of the women in the HBOT arm, who will be offered HBOT, will accept and undergo the treatment. As such, in the intervention arm, the overall proportion of women reporting moderate to severe pain will be 55% (0.5 × 30% + 0.5 × 80%) and 80% in the control group. In line with the TwiCs design, the control patients are not informed about the HBO treatment. Consequently, there will be no refusal in the control arm.

The purpose of this study is to evaluate if HBOT is either similar or better than usual care. Therefore, a directional (i.e., one-sided) test will be used. To demonstrate a significant difference of 55% vs. 80% with a power of 80%, a one-sided alpha of 0.05, and an inclusion ratio of HBOT vs. control group of 2:1, we need 72 patients in the HBOT arm and 36 patients in the control group. However, drop-out might be expected. These are not patients who refuse participation, but drop-out for other reasons, such as patients who no longer wish to participate in the UMBRELLA cohort or patients who accept the offer of HBOT, but drop-out afterwards. In order to adjust for 10% drop-out, a total of 120 (80:40) patients will be enrolled in the UMBRELLA HONEY trial. Enrollment is expected to take 20 months.

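### The QoL mixed model picks covariates by an imbalance rule that the article never describes; the cost is avoidable freedom in a secondary analysis, and a list fixed in advance would remove it

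*Protocol article*

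**What the plan says.** All the relevant text is in the Methods of the protocol article.

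- **QoL model (Data analysis).** QoL is analysed at three time points, two of them before treatment, with a random intercept, a random linear time effect and an AR(1) structure. On the fixed part it says "fixed effects for treatment arm and an interaction between time and treatment arm will be included", and then adds "as well as characteristics with imbalances as previously described".
- **Adjusted pain model (Data analysis, same paragraph, earlier).** As a sensitivity analysis, "the logistic regression analysis will be adjusted for age, time since radiotherapy, radiotherapy dose, and smoking". This list is fixed and carries no condition about imbalance.
- **Stratification (Randomization and informed consent).** "Randomization will be stratified for time since inclusion in the UMBRELLA cohort", cut at 2.5 years after the start of radiotherapy.
- **Status of QoL (Primary and secondary endpoints).** "Secondary endpoints include physical functioning, QoL, cosmetic outcome, physician-reported pain and radiation toxicity, tissue oxygenation, and side effects of HBOT".

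**The concern.** The phrase in the QoL model says two things: that covariates are selected because they are imbalanced, and that the selection has already been described. The latter does not check out. This is the only mention of imbalances in the article. Nothing before it gives candidate characteristics, a measure of imbalance, a threshold or a time of decision.

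Selection by imbalance is itself a weak principle. Between randomised arms, baseline imbalance arises by chance and says nothing about how strongly a characteristic predicts QoL. The rule can omit a prognostic characteristic that happens to balance and admit an irrelevant one that does not. Imbalance can only be seen in the trial's own data, so the model is settled after the groups have been compared. The adjusted pain analysis in the same paragraph follows the better principle, a list named in advance, and no reason is given for the difference.

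What is at stake is how far the QoL result could depend on an analyst's later choice of model.

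**Working it through.** The article gives no figure for the QoL model, so there is none to reproduce. The arm sizes used below do agree with its sample-size section: 72/0.9 = 80 and 36/0.9 = 40, 120 in all.

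**1. Look for what the back-reference points to.** Two earlier items could qualify.
- The four covariates of the logistic model: a fixed list, with no imbalance condition.
- The stratification factor: a design feature, not an imbalance rule.

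Neither describes how to find characteristics with imbalances.

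**2. How much does the model's content depend on the missing rule?** Inputs: 80 and 40 patients (article); the four covariates of the logistic model, treated as independent and normal (assumption); four candidate rules (assumption). The standard error of a standardised mean difference (SMD) is √(1/80 + 1/40) = √0.0375 = 0.194. The chance that at least one of four covariates is flagged, given perfect randomisation, is 1 − (1 − p)^4, where p is the chance per covariate.

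| Rule | p per covariate | At least one of four |
|---|---|---|
| P < 0.05 | 0.05 | 1 − 0.95^4 = 19% |
| P < 0.10 | 0.10 | 1 − 0.90^4 = 34% |
| SMD above 0.2 in absolute value | 2 × (1 − Φ(0.2/0.194)) = 0.302 | 76% |
| SMD above 0.1 in absolute value | 2 × (1 − Φ(0.1/0.194)) = 0.606 | 98% |

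These are chances of adding a covariate, not of bias. They show that the model's content depends on a rule the text does not supply.

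**3. Type I error.** Null simulation: 20,000 runs, 80:40, four independent covariates each correlated 0.2 or 0.3 with QoL, a linear model at one time point, and a two-sided 5% test. The correlations, the single time point and the two-sided test are assumptions.

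| Choice of covariates | Correlation 0.2 | Correlation 0.3 |
|---|---|---|
| All four, fixed in advance | 4.9% | 5.2% |
| Imbalance rule P < 0.05 | 4.5% | 4.2% |
| Imbalance rule SMD above 0.1 | 4.3% | 3.5% |
| Imbalance rule SMD above 0.2 | 4.1% | 3.1% |
| Most favourable of the 16 subsets | 9.6% | 14.0% |

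The simulation error near 5% is √(0.05 × 0.95/20,000) = 0.15 percentage points. A mechanical rule is therefore conservative. Only free choice of the most favourable subset inflates the error rate.

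**4. Size of the estimate, by contrast reported.**
- *Arm difference at one time point.* In the same simulation, the median spread of the estimate over the 16 subsets is 0.12 SD (correlation 0.2) to 0.18 SD (correlation 0.3).
- *The repeated-measures model the article describes.* A time-constant covariate entered as a main effect shifts a patient's expected QoL equally at every time point, so it drops out of a contrast of change over time. Simulation with common time points, a random intercept and slope, AR(1) errors and known covariance (all assumed) bears this out. The time-by-arm effect has a spread of 0 over the 16 subsets with complete data and about 0.01 SD with 10% missing follow-up. The arm difference at follow-up, not netted against the earlier time points, again spreads by about 0.16 to 0.20 SD.

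**The case against.** The strongest reply is that the back-reference has a natural target. The four covariates of the logistic model stand a few sentences earlier and are the only covariate list in the article. If all four were meant to enter regardless, nothing is chosen on the data, the two adjusted analyses already agree, and the flaw is editorial. That reading is possible. It does not rescue the wording, because the condition about imbalances leaves open whether all four enter or only those that look unequal, and by what measure.

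A second reply is that an article condenses a longer protocol, and that thresholds and coding belong in the full documents. That holds for detail on which an article is silent. Here the article states a selection principle and says it has been described, and the principle itself is the weaker one.

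Two stronger readings are tempting and are not supported.
- A reader might infer that the error rate of the QoL analysis is inflated. Step 3 shows a mechanical rule to be conservative. Inflation needs a free search for the most favourable subset, which the text does not provide for.
- A reader might infer that strong predictors of QoL are lost. QoL measured before treatment is already in the model as part of the repeated outcome, so the likeliest strong predictor is retained.

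It also stands that the time-by-arm interaction, if that is the reported effect, is almost immune to the choice.

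**Conclusion.** The point holds as a minor flaw in a secondary analysis. The article commits the QoL model to covariates chosen by imbalance, refers to a description that is not there, and so leaves avoidable freedom after the randomised groups have been seen.

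The size depends on the contrast reported: practically nil for time by arm, and roughly 0.1 to 0.2 SD for an arm difference at follow-up. These figures rest on assumed inputs: four independent covariates, correlations or effects of 0.2 to 0.3, and, for the mixed model, common time points and a known covariance structure. The article gives none of these values.

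The primary chi-square test, the unadjusted logistic regression and the logistic model with its fixed list are unaffected, and no sample-size figure changes.

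**What to change.** Delete the clause on imbalances and name the covariates. For example: the QoL model will also include age, smoking, radiotherapy dose and time since radiotherapy as fixed effects, irrespective of any baseline difference between the arms.

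Enter time since radiotherapy in a form that also carries the 2.5-year randomisation stratum. The two largely duplicate each other, so a separate stratum term is not needed. Use the same list and coding in the adjusted logistic model. Baseline pain (score 3 or 4) could be added to both, but this is optional.

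The cost is one sentence, settled before outcome data are examined by arm. It needs no new data: the four covariates are already planned for the pain analysis, and the pain score is collected for eligibility.
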